## Data analysis

Trial data will be transferred from paper case report forms (CRFs) to the electronic trial database, where it will be anonymised, but with preserved linkage records. Patient-identifiable data (PID) will be stored on a password-protected database within the Secure Data Hosting Service (SDHS) hosted by the University of Cambridge, with access granted only to relevant members of the trial team. PID will be kept for 5 years following the end of the trial, as per regulatory requirements. Participant consent will be specifically sought for data/sample sharing with our collaborators and use of remaining biological samples in future ethically approved research.

Data will be analysed on an ‘intention to treat’ basis, with further ‘per protocol’ analysis in participants with at least 80% compliance with trial medication. All endpoints will be summarised and broken down by treatment group and time point, where relevant. Mean, median, SD and minimum/maximum will be used for continuous endpoints and frequency tables for categorical or binary endpoints. Equivalent box and whisker plots or stacked bar charts will be produced for continuous and categorical endpoints, respectively.

The primary analysis will estimate the difference between treatment groups in terms of the primary endpoint. An analysis of covariance (ANCOVA) model will be fitted adjusting for baseline MDS-UPDRS gait/axial score, gender, LEDD and age. Treatment effect estimates, SEs, CIs (95% and 40% levels) and one-sided p values will be provided. A one-sided p value less than 25% will be regarded as statistically significant. Similar comparative analyses will be produced for other time points of the MDS-UPDRS gait/axial score and exploratory endpoints, using ANCOVA for continuous endpoints or logistic regression for categorical or binary endpoints.

Longitudinal data will use a mixed effect model repeated measurements (MMRM) analysis to include an unstructured patient-level random effect for nominal visit, visit and visit–treatment interaction fixed effects at visits post-baseline, with adjustment for baseline covariates. To assess the slope of change over time, the longitudinal data will be analysed using a similar MMRM but with a fixed effect of time from randomisation as a continuous, rather than nominal covariate, with a treatment–time interaction to compare treatment groups and patient-level random effect for slope, with adjustment for baseline covariates.

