#### Sample size calculation

The treatment effect size is unknown and therefore cannot be used to inform sample size calculations. A sample size of 60 has been selected pragmatically based on feasibility of recruitment.

However, longitudinal clinical data from the Incidence of Cognitive Impairment in Cohorts with Longitudinal Evaluation-PD (ICICLE-PD) cohort study provides some idea of an anticipated effect size for the primary outcome measure. ICICLE-PD patients were stratified by cytokine profile. Those with a ‘proinflammatory’ profile (n=32) had a more rapid symptom progression, with mean (SD) annualised change in MDS-UPDRS gait/axial score of 1.95 (1.92). In the subgroup with an ‘anti-inflammatory’ cytokine profile (n=26), mean (SD) annualised change in MDS-UPDRS gait/axial score was 0.72 (1.40).^12^ The corresponding between-group difference of 1.2 points is equivalent to a standardised effect size (Cohen’s d) of 0.73. The magnitude of this effect, which equates to a 4% change on the 28-point gait/axial MDS-UPDRS subscale, would be clinically significant. For comparison, the estimated minimum clinically important change on the full 132-point MDS-UPDRS motor scale is ≈2% (2.5 points).^43^ Furthermore, the axial-gait items of the MDS-UPDRS are those with the greatest impact on quality of life.^42^

As this is an early-phase proof of concept trial, it is important to maximise the chances of continuing development if the treatment is genuinely effective, and thus a significance level of 25% under a one-sided test will be used. If the treatment effect is a 2% change (0.37 standardised effect), the design has 78% power, and for a 4% change (0.73 standardised effect), the design has 99% power.

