### Treatment allocation, blinding and safety monitoring

Participants will be randomised 1:1 to receive azathioprine or placebo using Sealed Envelope, an online randomisation system. Clinical assessors and participants will be blinded to treatment allocation. Balanced assignment of each treatment will be achieved using permuted block randomisation, which will be stratified for: age ≤71 versus >71, and MDS-UPDRS-III ≤30 versus >30.

Treatment will be commenced at a dose of 1 mg/kg, based on 25 mg tablets of IMP (azathioprine/placebo). In addition to the visits shown in figure 1, treatment monitoring visits will be conducted to screen for potential complications associated with azathioprine. These will include blood tests to screen for myelosuppression, liver or renal dysfunction, AEs reporting and assessment of treatment compliance (review of patient-completed dosing diary and counting of the investigational medicinal product (IMP) at regular intervals). Initially, monitoring visits will occur 2 weekly, and after 4 weeks, the azathioprine dose will be increased to 2 mg/kg (assuming blood tests and clinical assessments are satisfactory), the standard therapeutic dose used in clinical practice. There will be a matched doubling of the placebo dose to maintain blinding. Once the participant is stable on their dose, treatment monitoring will be carried out less frequently (see monitoring protocol, figure 3).

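### The primary ANCOVA leaves out one of the two randomisation strata (MDS-UPDRS-III), which may make the 25% test slightly conservative

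*Protocol article*

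**What the plan says.** The section on treatment allocation, blinding and safety monitoring in the protocol article sets 1:1 allocation by permuted blocks, "stratified for: age ≤71 versus >71, and MDS-UPDRS-III ≤30 versus >30".

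The Data analysis section fixes the primary model: "An analysis of covariance (ANCOVA) model will be fitted adjusting for baseline MDS-UPDRS gait/axial score, gender, LEDD and age". The decision rule is "A one-sided p value less than 25% will be regarded as statistically significant", which matches the Sample size calculation section, where "a significance level of 25% under a one-sided test will be used".

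On size and power, the Sample size calculation section says: "A sample size of 60 has been selected pragmatically based on feasibility of recruitment". It adds: "If the treatment effect is a 2% change (0.37 standardised effect), the design has 78% power". At the larger standardised effect of 0.73, the power it states is 99%.

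Two other statements bear on the point. The Outcome measures section defines the gait/axial score as the sum of seven items of MDS-UPDRS part III. The Data analysis section says that the mixed models adjust for baseline covariates, without listing them.

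**The concern.** A factor that restricts the randomisation normally belongs in the analysis model. Blocking within the MDS-UPDRS-III stratum makes the arms alike on it, so the stratum contributes little to the real sampling variation of the treatment difference. If it also predicts outcome and is left out of the model, its contribution stays in the residual variance. The reported standard error is then larger than the true one, the intervals are a little wide, and the test runs below its nominal level.

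Here the model includes age, one of the two stratification factors, together with gender and LEDD, which are not stratified. It omits the other stratification factor and gives no reason. The covariates are listed explicitly, so this is a stated choice and not a detail left open.

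What is at stake is the use made of the 25% level. The article chose it to keep a good chance of continuing development if the drug works, and a test that runs below 25% works slightly against that aim. With 60 participants fixed by feasibility, precision is more easily gained in the model than by recruiting more people.

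**Working it through.** **Inputs from the article.** 60 participants at 1:1, so 30 per arm. One-sided alpha 0.25, critical value 0.6745. Standardised effects d = 0.37 and 0.73. Annualised change in the reference cohort: mean 1.95 (SD 1.92) and 0.72 (SD 1.40).

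**Assumption.** Let r be the share of residual variance, after the listed covariates, that the MDS-UPDRS-III stratum explains. The article does not give r, so a range is used.

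**Step 1: reproduce the stated figures.**
- Effect: (1.95 − 0.72) / √[(1.92² + 1.40²)/2] = 1.23/1.68 = 0.73.
- Power = Φ(d/√(2/30) − 0.6745) = Φ(d√15 − 0.6745).
- d = 0.37: Φ(1.433 − 0.6745) = 77.6%, against 78% stated.
- d = 0.73: Φ(2.827 − 0.6745) = 98.4%, against 99% stated.

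Both agree to within a point. The calculation uses raw SDs of change and takes no credit for covariate adjustment.

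**Step 2: large-sample effect of the omission.** Set the residual SD of the listed model to 1, and suppose that blocking removes the stratum entirely from the sampling error. The reported SE is √(2/30) and the true one is √(1−r)·√(2/30), so the inflation is 1/√(1−r). Then:
- type I error, stratum omitted: 1 − Φ(0.6745/√(1−r))
- power, omitted: Φ(d√15/√(1−r) − 0.6745/√(1−r))
- power, included: Φ(d√15/√(1−r) − 0.6745)

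| r | SE inflation | Type I error, omitted | Power at 0.37, omitted | Power at 0.37, included |
|---|---|---|---|---|
| 0 | 0% | 0.2500 | 77.6% | 77.6% |
| 0.02 | 1.0% | 0.2478 | 77.8% | 78.0% |
| 0.05 | 2.6% | 0.2445 | 78.2% | 78.7% |
| 0.10 | 5.4% | 0.2385 | 78.8% | 79.8% |
| 0.20 | 11.8% | 0.2254 | 80.2% | 82.3% |

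At d = 0.73 the difference between the two models is at most 0.2 points.

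**Step 3: simulation at N = 60.** There were 20,000 trials per setting, with four strata and an assumed block size of 4. The model contained the listed covariates, and the assumed correlation between gait/axial score and part III was 0.5, 0.7 or 0.85. At r = 0.10:

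| Correlation | Reported SE, omitted | Actual SD, omitted | Ratio | Type I error, omitted | Power, omitted | Power, included |
|---|---|---|---|---|---|---|
| 0.5 | 0.2654 | 0.2567 | 1.034 | 0.2413 | 77.1% | 78.4% |
| 0.7 | 0.2646 | 0.2556 | 1.035 | 0.2384 | 76.7% | 78.1% |
| 0.85 | 0.2647 | 0.2596 | 1.020 | 0.2444 | 76.7% | 78.3% |

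The SE is 2% to 4% too wide, less than the formula's 5.4%, because blocking in small strata does not remove the stratum completely. The gain from including the term is 1.3 to 1.6 points at r = 0.10 and about 0.5 points at r = 0.05. At r = 0 the reported SE is right to within simulation error, and adding the term lowers power by 0.1 to 0.2 points (about 0.1).

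**The case against.** The strongest reply is that the gait/axial baseline already does much of the work. It consists of seven part III items worth 28 of the 132 points, so the model carries part of the stratum's information. This stands, and it limits the size of the effect. In a simulation that assumed a median split and an outcome linear in part III, a stratum explaining 10% of outcome variance on its own explained only about 7%, 4% or 2% after gait/axial adjustment, at correlations of 0.5, 0.7 and 0.85. A stratum explaining 20% on its own fell to about 15%, 9% and 4%. If change depends only on the gait/axial baseline, the remaining share is zero. The stand-in is partial, however, because the other 104 points of part III are not in the model.

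The second reply is that nothing is invalid. That stands too. The estimate is unbiased, the test does not exceed its 25% level, and the estimator keeps most of the benefit of blocking: its actual SD at r = 0.10 is 0.256 to 0.260, against 0.252 to 0.254 with the term included.

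A reader might also infer two further faults that the text does not establish.
- *The mixed models omit the stratum too.* They are said to adjust for baseline covariates that are not listed, so omission there is not shown.
- *LEDD is a follow-up value.* The wording could be tightened, but the later reference to baseline covariates points to baseline, and this point does not depend on it.

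**Conclusion.** The mismatch between design and analysis is plain in the text: one of two stratification factors is missing from the primary model. Its consequence is conditional and small. The test is conservative only to the extent that the MDS-UPDRS-III stratum predicts 12-month change beyond gait/axial score, gender, LEDD and age, and the article gives no figure for that. For an assumed residual share of up to 10%, the cost at d = 0.37 is about one power point (1.0 by formula, up to 1.6 in simulation). At 20% it is about two points by formula. At d = 0.73 it is negligible.

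A reader might conclude that the standard error is certainly too wide, that the stated power is overstated, or that the benefit of stratifying is lost. The documents support none of these. The first depends on an unknown quantity. The 78% and 99% rest on raw SDs without covariate adjustment and reproduce as they stand. The balance from blocking remains in the estimate even when the model does not credit it. Severity is minor.

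**What to change.** Add baseline MDS-UPDRS-III to the covariates of the primary ANCOVA, either as the ≤30/>30 stratum or as the continuous score, chosen in advance, and keep age. Otherwise, state why it is left out. Use the same covariate set wherever the mixed models adjust for baseline covariates, so that the analyses agree.

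The cost is one degree of freedom and a line of text. No new data are needed, because the MDS-UPDRS is scheduled at the baseline visit, where randomisation also takes place. If the stratum turns out not to be prognostic, the loss is about 0.1 power point. The article states that recruitment had not begun and that amendments were expected, so the term could be specified before any outcome data exist.

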## Methods and analysis

### Overview

AZA-PD is a randomised, double-blind, placebo-controlled trial of azathioprine in early PD that aims to provide ‘proof of concept’ that a peripherally acting immunosuppressive drug can slow clinical disease progression. The trial will investigate whether the drug has an effect on disease course over 12 months of treatment and whether this is maintained over 6 months of subsequent follow-up. Sixty participants will be recruited and randomised 1:1 to receive active treatment or placebo. Clinical assessments will be performed at baseline, 6 months, 12 months and 18 months (6 months postcompletion of treatment), with rigorous safety monitoring. In addition, the trial aims to demonstrate ‘proof of mechanism’ by evaluating the impact of azathioprine on blood, CSF and neuroimaging parameters of immune activation in the trial population and determining the relationship between these parameters and clinical measures of disease progression.

The trial timeline is summarised in figure 1.

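### The 40% confidence interval reported beside the one-sided 25% test does not correspond to that test; the two-sided interval that does is 50%

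*Protocol article*

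**What the plan says.** The sample size section of the protocol article sets the type I error: "a significance level of 25% under a one-sided test will be used". The Data analysis section repeats it as the criterion for the primary endpoint: "A one-sided p value less than 25% will be regarded as statistically significant". The sentence just before that one lists what will be reported from the same ANCOVA: "Treatment effect estimates, SEs, CIs (95% and 40% levels) and one-sided p values will be provided".

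The article gives no reason for the 40% level and no rule for reading that interval. The same section plans similar comparisons for other time points and for the exploratory endpoints.

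**The concern.** A one-sided test at level α and a two-sided interval at level 1 − 2α give the same answer on whether zero is excluded on the benefit side. With α = 0.25 that interval is 50%, not 40%. A 95% interval is a familiar descriptive choice. A second, unusually low level placed beside a relaxed α has no evident purpose except to mirror the test, and readers will use it that way.

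The stake is how a borderline result reads. The mismatch runs in one direction only: the printed interval can suggest benefit when the test has not reached significance. That matters in a proof-of-concept trial, where the 25% level was chosen with continued development in mind. If the same two levels are carried over to the other endpoints, the mismatch recurs there.

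**Working it through.** **Inputs.** One-sided α = 0.25 (Sample size calculation; Data analysis). Interval levels 95% and 40% (Data analysis). Sixty participants randomised 1:1, so 30 per arm (Overview). Standardised effects 0.37 and 0.73 with stated power 78% and 99% (Sample size calculation). Cohort SDs of annualised change 1.92 and 1.40 (same section).

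**1. Reproduce the stated power, to see which α the design uses.** For two means with n per arm, power = Φ(d√(n/2) − z), where z is the 1 − α normal quantile. With n = 30, √15 = 3.873.

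- d = 0.37: noncentrality 0.37 × 3.873 = 1.433. At α = 0.25, Φ(1.433 − 0.674) = 77.6% (77.5% with a noncentral t), against 78% stated. At one-sided 0.30, Φ(1.433 − 0.524) = 81.8%. At two-sided 0.25 it is 61.1%.
- d = 0.73: noncentrality 2.827. At α = 0.25 power is 98.4%, and at 0.30 it is 98.9%, against 99% stated. Both are close, so this scenario does not separate the two levels.

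The 78% figure does separate them. It fits 25% one-sided and not 30%. The design α is therefore 25%, and the 40% interval level is the figure out of line.

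**2. Match interval to test.**

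- The two-sided level matching α = 0.25 is 1 − 2 × 0.25 = 50%, with multiplier 0.674.
- The one-sided α matching a two-sided 40% interval is (1 − 0.40)/2 = 0.30, with multiplier 0.524.
- Read instead as a one-sided 40% bound, it would match α = 0.60.

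No standard reading leads from 40% to 25%. The ratio is 0.524/0.674 = 0.78, so the 40% interval is 22% narrower than the matching one. With t quantiles on 54 residual degrees of freedom (60 participants, four covariates, treatment and intercept) the multipliers are 0.528 and 0.679, again 22%.

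**3. Where they disagree.** The 40% interval excludes zero on the benefit side when one-sided p < 0.30; the test needs p < 0.25. They disagree for p from 0.25 to 0.30, whatever the SD. The probability is Φ(0.674 − δ) − Φ(0.524 − δ), with δ the noncentrality:

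| True standardised effect | δ | Probability of disagreement |
|---|---|---|
| 0 | 0 | 5.0% |
| 0.37 | 1.433 | 4.2% |
| 0.73 | 2.827 | 0.5% |

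**4. Illustration in points (assumed SD).** Taking the root mean square of the cohort SDs, √((1.92² + 1.40²)/2) = 1.68, the standard error is 1.68 × √(2/30) = 0.434. The 40% interval excludes zero from 0.524 × 0.434 = 0.23 points of benefit; the test needs 0.674 × 0.434 = 0.29. An observed benefit of 0.26 points has p = 0.275, a 40% interval of 0.03 to 0.49 and a 50% interval of −0.03 to 0.55.

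**The case against.** The strongest reply is that the 40% interval decides nothing. The article lists it among reported quantities, and the only criterion is the p value. A reader might infer that the trial would be judged on the 40% interval, that interval and test could return opposite verdicts, or that the true false-positive rate is 30%. The documents support none of these: no sentence says that the 40% interval must exclude zero. A 30% error rate arises only if someone sets the stated criterion aside. This part of the reply stands, and it limits the weight of the point.

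A second reply is that the 95% interval does not match the test either. By the same reasoning it includes zero while the test is significant for one-sided p from 0.025 to 0.25: 22.5% of trials under the null, and about 48% at d = 0.37 (Φ(1.960 − 1.433) − Φ(0.674 − 1.433) ≈ 0.70 − 0.22). This shows that a reported interval need not correspond to the test, and the 95% interval needs no change. It does not rescue the 40% level, because 95% is read by convention as descriptive and 40% has no such convention behind it.

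A third reply is that the purpose of the 40% interval may be explained in an analysis plan that is not shown. That is possible, and the missing explanation is not the point raised here. The point is that the level stated in the article does not fit the test stated beside it.

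**Conclusion.** The mismatch is real, and its weight is minor to moderate. A 40% two-sided interval corresponds to a one-sided 30% test, while the plan tests at 25% in both places where it states a level, and its 78% power figure agrees with 25%. The p value alone governs, so the formal decision, type I error and power are untouched. What is affected is presentation: for one-sided p between 0.25 and 0.30 the printed interval excludes zero in favour of azathioprine beside a non-significant test.

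The p-value range of the disagreement needs no assumption about the SD. The probabilities use a normal approximation with 30 analysed per arm; with a t distribution the figure at d = 0.37 is 4.3% rather than 4.2%. The thresholds of 0.23 and 0.29 points rest on an assumed unadjusted SD of 1.68 from the cohort data. The planned ANCOVA adjusts for covariates, so its standard error may differ. That the 40% level was meant to mirror the test is an inference, since the article does not say so.

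**What to change.** In Data analysis, replace the 95% and 40% levels with 95% and 50%, or report a one-sided 75% confidence bound beside the 95% interval. Add one sentence saying that the 50% interval (or 75% bound) corresponds to the one-sided 25% test and that the 95% interval is descriptive. Carry the same levels through to the other time points and exploratory endpoints, and align the statistical analysis plan.

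If 40% was deliberate, state its purpose and say that it is descriptive and does not correspond to the significance criterion.

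The cost is one number and one sentence, with no effect on sample size, power or trial conduct. The change should be made before any unblinded outcome data are seen.

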### Outcome measures

The primary outcome measure is change in MDS-UPDRS gait/axial score in the OFF state over the 12-month treatment period. This is a clinical measure that has been shown to be the most sensitive measure of motor progression in PD, is relatively resistant to dopaminergic therapy and has an important impact on quality of life.^42^ This score is a sum of the points from the following sections of MDS-UPDRS part III:

3.1 – speech.3.2 – facial expression.3.9 – rising from a chair.3.10 – gait.3.12 – postural stability.3.13 – posture.3.14 – body bradykinesia.

Other outcome measures are exploratory and include:

Change in MDS-UPDRS gait/axial score in OFF state at 18 months.Change in total MDS-UPDRS in OFF state at 12 and 18 months.Change in electromagnetic sensor (EMS) measurements while performing MDS-UPDRS tremor and bradykinesia assessments at 12 and 18 months.Proportion of patients developing postural instability (Hoehn and Yahr stage 3 or greater) at 12 and 18 months.Change in global cognition (Addenbrooke’s Cognitive Examination-III (ACE-III))) at 12 and 18 months.Change in patient-reported outcome measure of quality of life (Parkinson’s Disease Questionnaire 39 (PDQ-39)) at 12 and 18 months.Change in Non-Motor Symptom Scale (NMSS) at 12 and 18 months.Change in dose of symptomatic dopaminergic therapy (Levodopa Equivalent Daily Dose (LEDD)) at 12 and 18 months.The safety and tolerability of azathioprine assessed by the number of adverse events (AEs) recorded during the 12-month treatment period.Change in [^11^C]-PK11195 PET non-dissociable binding potential (BP_ND_) in subcortical and cortical regions of interest at 12 months.Change in total lymphocyte count at 6, 12 and 18 months.Change in serum immunoglobulin levels at 6, 12 and 18 months.Change in levels of serum and CSF cytokine levels at 12 and 18 months.Change in lymphocyte subsets in blood and CSF at 12 and 18 months.

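### The one-sided 25% significance rule is not confined to the primary endpoint, and the test direction is undefined for adverse events and immune markers

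*Protocol article*

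**What the plan says.** The Sample size calculation section introduces the level with a development argument: in an early-phase trial "it is important to maximise the chances of continuing development if the treatment is genuinely effective". From this argument the section draws the level itself: "thus a significance level of 25% under a one-sided test will be used". The power figures that follow (78% and 99%) use standardised effects of 0.37 and 0.73, both expressed as changes on the gait/axial score, which is the primary outcome.

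The Data analysis section describes the primary ANCOVA and its outputs: "Treatment effect estimates, SEs, CIs (95% and 40% levels) and one-sided p values will be provided". It then sets the decision rule: "A one-sided p value less than 25% will be regarded as statistically significant". Immediately afterwards comes the extension: "Similar comparative analyses will be produced for other time points of the MDS-UPDRS gait/axial score and exploratory endpoints". The models named for these are ANCOVA and logistic regression. No other threshold is stated, and neither is a direction of test.

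The Outcome measures section introduces the remaining outcomes with "Other outcome measures are exploratory and include" and lists 14 items. Several have more than one time point, for example "Change in total lymphocyte count at 6, 12 and 18 months". One item is safety: "The safety and tolerability of azathioprine assessed by the number of adverse events (AEs) recorded during the 12-month treatment period".

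**The concern.** The 25% level is a deliberate trade for one decision. The sponsor accepts a one-in-four chance of taking an ineffective drug forward in return for a small chance of dropping an effective one. That argument belongs to the primary endpoint. It says nothing about cytokines, PET binding, cognition or adverse events, and nothing in the article makes the argument for them.

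The article also aims to show proof of mechanism from blood, CSF and imaging. If the rule is followed as written, those results and the secondary clinical results could be reported as statistically significant at a level that chance alone reaches one time in four.

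A one-sided test also needs a direction. For a clinical score this is obvious. For total lymphocyte count it is not: a fall is the intended pharmacological effect (Introduction), while significant myelosuppression is among the grounds for dose reduction or withdrawal (Treatment allocation, blinding and safety monitoring). For adverse events, a test pointing towards benefit would not flag an excess on azathioprine.

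**Working it through.** **1. Reproduce the plan's own figures.** Inputs from the article: 60 participants, 1:1, so 30 per arm; one-sided level 0.25, so z = 0.674; effects d = 0.37 and 0.73. Power = Φ(d × √(30/2) − 0.674).

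- d = 0.37: 0.37 × 3.873 = 1.433; Φ(0.759) = 0.776, against the stated 78%.
- d = 0.73: 0.73 × 3.873 = 2.827; Φ(2.153) = 0.984, against the stated 99%.

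Both agree to within a percentage point. A two-sided 25% test would give 61% and 95%, so the one-sided reading is the one the design uses, and it was sized on the primary outcome.

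**2. How little is needed to cross the threshold.** Without covariate adjustment, one-sided p < 0.25 is reached at an observed difference of 0.674 × √(2/30) = 0.17 SD.

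**3. Count the exploratory comparisons**, one per listed outcome and time point:

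| Outcome | Comparisons |
|---|---|
| Gait/axial score, 18 months | 1 |
| Seven outcomes at 12 and 18 months (total MDS-UPDRS, EMS, postural instability, ACE-III, PDQ-39, NMSS, LEDD) | 14 |
| Adverse events | 1 |
| PET | 1 |
| Lymphocyte count, 6/12/18 months | 3 |
| Immunoglobulins, 6/12/18 months | 3 |
| Cytokines, 12/18 months | 2 |
| Lymphocyte subsets, 12/18 months | 2 |
| **Total** | **27** |

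Counting CSF separately from serum or blood adds 4, giving 31. Table 1 shows no CSF collection at 18 months, which removes 2 and gives 29. Individual cytokines, cell subsets, PET regions, the 6-month gait/axial comparison and the per-protocol repeat are not counted.

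**4. Expected chance findings if every null were true.** Expected number = k × 0.25: 27 × 0.25 = 6.75, and 31 × 0.25 = 7.75. Expectations add whatever the dependence, so correlation does not change these figures.

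**5. Allow for real immune effects.** If all 11 immune and imaging comparisons (3 + 3 + 2 + 2 + 1) reflected true changes, 16 comparisons would remain, and 16 × 0.25 = 4.

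**6. Probability of at least one, and of three or more, with k = 27 and all nulls true.** The article gives no correlations, so a range is assumed. The zero row is exact (1 − 0.75^27 = 0.9996); the others are simulated with equal correlation between all test statistics.

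| Assumed correlation | P(≥1) | P(≥3) |
|---|---|---|
| 0 | 99.96% | 97.9% |
| 0.1 | 99% | 90% |
| 0.3 | 93% | 75% |
| 0.5 | 83% | 63% |
| 0.7 | 68% | 52% |

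With correlation 0.7 between time points of the same outcome and 0 to 0.3 between outcomes, three or more has probability 95% down to 74%.

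**The case against.** **The carry-over is inferred.** The threshold sentence sits in the paragraph that opens with the primary analysis, and the extension goes on to name models. It could mean similar modelling and outputs, not the same decision rule. Thresholds for exploratory endpoints are often left to the SAP, which is not shown. This stands as a limit on the wording: no sentence applies 25% to the exploratory outcomes. It does not remove the point, because the article itself states an unrestricted rule and then extends the analyses in the next sentence.

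**Exploratory outcomes need no multiplicity control.** Agreed. The absence of adjustment is normal in a phase II trial and is not criticised here. The defect is that a significance label at 25% is left available for these outcomes.

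**Adverse events may not be covered.** They are in the exploratory list, but the outcome is a count with no baseline value, which fits neither of the named models neatly. They may be intended only for the summaries by arm. The text does not settle this.

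**Two stronger readings go too far.** A reader might infer that several false positives are almost certain. That needs near-independence and all nulls true. The outcomes overlap and repeat over time, and the article expects azathioprine to change blood count parameters. A reader might also infer that harm goes untested. The documents do not support that: the planned 95% CIs show effects in either direction, all endpoints are summarised by treatment group, a DSMB sees interim safety data, and an unblinded team reviews the monitoring bloods.

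**Conclusion.** The point holds in a limited form. The article does not confine the one-sided 25% rule to the primary endpoint, and its natural though not explicit reading extends the rule to 27 exploratory comparisons (29 to 31 with CSF separated). The stated rationale covers only the decision to continue development.

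Under the global null about 7 comparisons would be labelled significant by chance, whatever their correlation. This is an upper-end figure; about 4 would be expected if every immune and imaging comparison reflected a real change and no other outcome differed. The chance of three or more depends on correlations the article does not give, and ranges from 52% to 98% over those assumed here.

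Separately, the direction of the one-sided test is undefined for adverse events and immune markers. If the test for adverse events pointed towards benefit, it would not flag excess harm; detection would then rest on the CIs, the summaries by arm and DSMB review. The primary analysis is not affected.

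**What to change.** - Add to the 25% sentence in Data analysis: *for the primary endpoint at 12 months only*.
- Report all other endpoints and time points as estimates with the two-sided 95% CIs already planned, labelled exploratory and not declared statistically significant at the 25% level.
- Compare adverse events between arms two-sided.

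For scale, under the global null 27 × 0.05 = 1.35 of the 95% CIs would be expected to exclude no difference in either direction, against 6.75 labels under the 25% rule. A different stated threshold for exploratory outcomes would also remove the ambiguity, but estimates with CIs suit their exploratory status and need no new output.

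The cost is wording only: sample size, visits and the primary test are unchanged. The sponsor gives up the 25% significance label on exploratory results.
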